## Abstract

**Introduction:**

Musculoskeletal pain is the second leading cause of disease burden in Australia, and there is a need to investigate new models of care to cope with the increasing demand for health services. This paper describes the protocol for a randomised controlled trial investigating whether a physiotherapist-led triage and treatment service is non-inferior for improving function at 6 months and superior for reducing treatment waiting times, compared with usual care for patients with musculoskeletal pain referred to public hospital outpatient physiotherapy clinics.

**Methods and analysis:**

A total of 368 participants (184 per arm) will be recruited from six public hospitals located in metropolitan Sydney, Australia. We will recruit adult patients newly referred to a public hospital physiotherapy outpatient clinic with a musculoskeletal condition that is typically managed by a physiotherapist (eg, back or neck pain, osteoarthritis, rehabilitation postorthopaedic surgery and sporting injuries). Participants will be randomised 1:1 to the physiotherapist-led triage and treatment service or usual care. A physiotherapist will telephone participants in the intervention group and match them to different modes and types of care based on baseline characteristics. Participants at low risk of poor outcomes (assessed by the Keele STarT MSK tool) will be given simple advice and education during this call and instructed to call back if their symptoms do not improve in 6 weeks. Participants at medium risk of poor outcomes or requiring postoperative rehabilitation will be offered a course of telehealth (videoconference) physiotherapy targeting exercise-based self-management. Participants at high risk of poor outcomes and/or with potential nonprogressive radiculopathy will be offered a course of usual clinic-based physiotherapy as per all participants in the usual care group. Physical function (Patient Specific Functional Scale) at 6 months postrandomisation and waiting time (time from randomisation to first treatment) are coprimary outcomes. Secondary outcomes include other patient outcomes (eg, pain), health resource use, adverse events, process measures (eg, adherence) and costs.

**Ethics and dissemination:**

This trial has approval from the Sydney Local Health District Human Research Ethics Committee (RPAH Zone; X24-0090 and 2024/ETH00585). Recruitment will commence in September 2024 and is expected to be completed by December 2025 with follow-ups completed by December 2026. The results of the trial will be submitted for publication in reputable international journals and presented at relevant national and international conferences.

**Trial registration number:**

ANZCTR (ACTRN12624000947505).

STRENGTH AND LIMITATIONS OF THIS STUDYThis is a multicentre, two-arm, parallel-group randomised controlled trial with nested process and economic evaluation.Findings may provide information on the implementation of a physiotherapist-led triage and treatment service that could improve access to care within outpatient hospital physiotherapy departments.Participants will be blinded to the study hypothesis.Physiotherapists delivering the interventions will not be blinded.All study sites will be in metropolitan Sydney, so the findings might not be applied to rural and remote parts of Australia or other countries.

## Introduction

 Musculoskeletal pain is the second leading cause of disease burden in Australia, and there is a need to investigate new models of care to cope with the increasing demand placed on health services.^1 2^ Many Australians seeking care for musculoskeletal pain do not have private health insurance^3^ and join increasingly long waiting lists for clinic-based physiotherapy in publicly funded hospitals (where there is no cost to the patient). Long waiting times of up to 12 months^4^ for physiotherapy in public hospitals likely delay recovery for some patients with musculoskeletal pain and lead some to develop persistent disabling symptoms that are costly and complex to manage.^5^,^7^ A potential solution to reduce treatment waiting times is a model of care that can identify patients with simple musculoskeletal problems that can be managed with less resources (eg, brief telephone appointments and App-based home exercise programmes), thereby freeing up clinic-based resources for patients with more complex presentations.

A promising model of care that reduced treatment waiting times without compromising clinical outcomes in a large randomised controlled trial (RCT; n=2256) was the UK PhysioDirect telephone assessment and advice service for patients with musculoskeletal pain.^8^ PhysioDirect used an innovative clinical algorithm that supported physiotherapists to triage patients who needed clinic-based care while managing patients they judged to be able to self-manage via telephone consultation (exercise advice and advice leaflets).^8^ PhysioDirect reduced treatment waiting times compared with usual clinic-based care (median of 7 days vs 34 days, arm time ratio of 0.32, 95% CI 0.29 to 0.35) and was deemed equally clinically effective and seemingly safe.^8^ It was also acceptable to patients and physiotherapists in the UK.^8^

The PhysioDirect model of care inspired us to develop and evaluate a similar model of care to tackle the long waiting times in many outpatient physiotherapy clinics in Australia. Our initial ‘triage and treatment service’ was developed for a multidisciplinary rheumatology and physiotherapy clinic where it was later evaluated in a pilot and feasibility RCT for people with low back pain.^9^ In this trial, a rheumatologist called participants in the intervention group soon after they joined the clinic waiting list and matched them to different modes and types of care based on a baseline screening assessment. Participants at low risk of poor outcomes (assessed by the Keele STarT MSK tool)^10^ were given simple advice and education during this call and instructed to call back if their symptoms did not improve in 6 weeks. Participants at medium and high risk of poor outcomes were offered a course of telehealth (videoconference) physiotherapy targeting exercise-based self-management. High-risk participants were additionally encouraged to complete an online self-directed pain education programme. Participants with potential nonprogressive radiculopathy were offered a clinic-based rheumatology appointment with the option of clinic-based physiotherapy. Findings from the pilot and feasibility RCT and additional qualitative interviews were used to refine our new model of care and adapt it for use in outpatient physiotherapy clinics (‘physiotherapist-led triage and treatment service’) that manage a range of musculoskeletal conditions. A more detailed description of the development and refinement of our physiotherapist-led triage and treatment service is described elsewhere.^11^

This paper describes the protocol for an RCT (WAIT-less trial) investigating whether our new physiotherapist-led triage and treatment service is noninferior for improving function at 6 months and superior for reducing treatment waiting times (coprimary outcomes) compared with usual clinic-based physiotherapy care for patients with musculoskeletal pain referred to public hospital outpatient physiotherapy clinics.

## Methods and analysis

### Design

The WAIT-less trial is a pragmatic multicentre, two-arm, parallel-group RCT with nested process and economic evaluation. This protocol follows the Standard Protocol Items: Recommendations for Interventional Trials statement (https://www.spirit-statement.org/). The trial is registered with the Australian and New Zealand Clinical Trials Registry—trial registration number ACTRN12624000947505.

### Setting

The WAIT-less trial will be conducted in several public hospital outpatient physiotherapy clinics across Sydney Local Health District (SLHD) and South Eastern Sydney Local Health District (SESLHD) in NSW, Australia, and compare the physiotherapist-led triage and treatment service with usual clinic-based care. The participating hospitals provide diversity with respect to patient demographic characteristics, ethnicity, hospital setting and outpatient clinic staffing models. We will randomise, across all sites, 368 participants to this trial (ie, 184 per arm). Participants in the physiotherapist-led triage and treatment service group and usual care group will be treated at the hospital they are referred to.

### Eligibility criteria

Patients referred to participating outpatient physiotherapy clinics are referred from Hospital Emergency Departments, inpatient units, outpatient hospital clinics and local General Practices. Occasionally, patients can self-refer but only at some hospitals and in extenuating circumstances. Potentially eligible newly referred patients will be contacted by a screening physiotherapist from either an SLHD or SESLHD site to determine if the patient is eligible and interested in participating in the trial. Figure 1 illustrates the trial design. Box 1 below describes the eligibility criteria for the trial.

**Figure 1 F1:**
[figure not shown]
Trial design.

Box 1Eligibility criteriaInclusion criteriaAdult patient (≥18 years)New referral (defined as being referred within the last 6 weeks) to a public hospital physiotherapy outpatient clinic with a musculoskeletal condition or musculoskeletal pain (hereafter referred to as ‘musculoskeletal pain’) that would usually be managed by a physiotherapist. Examples include but are not limited to:Back/neck painOsteoarthritisWhiplash-associated disordersAnkle sprainsPostfractureSporting injury (eg, ankle sprains)Postorthopaedic surgery (eg, hip or knee replacement, rotator cuff repair)Willing to participate and provide follow-up dataCan speak and read English to provide informed consentExclusion criteriaSuspected serious underlying pathology or musculoskeletal conditions requiring urgent medical care (eg, malignancy, fracture, infection, inflammatory arthritis and joint dislocation)New referral strongly suggestive of concerning neurological features (eg, progressive radiculopathy or upper motor neuron lesion)Is on a postoperative exercise regimen prescribed by a surgeon which specifies the mode of care delivery (eg, needs to be provided in a clinic supervised by a physiotherapist)Requiring mobility progression or assistance weaning from a walking aid(s) whereby the person is at an increased fall risk and needs to be seen in the clinicPregnant women.

### Participant recruitment

Initial contact with patients referred to the outpatient physiotherapy clinic will be made as soon as possible after a referral is received by a screening physiotherapist via telephone. During this call, patients will be invited to participate in the trial. If patients demonstrate interest, the screening physiotherapist will explain the trial and determine their eligibility using a screening form that contains the eligibility criteria. For all patients interested and eligible to be involved, the screening physiotherapist will send an email, SMS or mail out of the trial information pack that includes the Participant Information Statement Form (online supplemental appendix 1), Participant Consent Form (PCF—online supplemental appendix 2) and the baseline assessment questionnaire. Participants will be made aware that participation is voluntary, and they are free to withdraw at any time with no repercussions. Participants who receive the information pack via email or SMS will provide consent by ‘checking’ a radio button in an online survey through Research Electronic Data Capture (REDCap) and then proceed to the baseline assessment questionnaire online. For all interested and eligible patients who are not able to complete the PCF and baseline assessment questionnaire via SMS or email, they will be sent the trial information pack via post. Patients who receive the trial information pack via post will be provided with a pen and a postage-paid return envelope, so they can post their signed PCF and completed baseline assessment questionnaire to the screening physiotherapist.

The screening physiotherapist will offer all participants a telephone call if they need assistance completing the PCF or baseline assessment questionnaire. Participant consent will be documented in the REDCap trial database and the participant’s hospital medical record. This is as per normal practice and a medico-legal requirement. All patients deciding not to be involved in the trial will receive care from a health practitioner as per the standard of care in the clinic they were referred to. At any time during the study if the treating physiotherapist determines serious pathology must be excluded (suspicion of red flag pathology via assessment and screening questions), the participant will be referred to their general practitioner or referring doctor (eg, orthopaedic surgeon, rheumatologist or within hospital specialty) to obtain medical clearance before resuming physiotherapy as per best practice.

### Randomisation procedure

The 1:1 random allocation sequence will be independently generated in Stata by the team’s biostatistician and uploaded to REDCap. Allocation will be concealed as the biostatistician generating the sequence will not be involved in the recruitment of participants and the screening physiotherapist will not know the participant’s group allocation until their baseline data are entered into REDCap. The allocation sequence will also be concealed from potential participants and all on-site staff associated with the trial. The randomisation sequence will use randomly permuted blocks of variable sizes (2 and 4) to ensure equal numbers in both groups. Stratification variables for the randomisation sequence include trial sites and the three treatment subgroups. This will ensure that the intervention and control groups have a similar proportion of participants across different trial sites. The screening physiotherapist will telephone participants who consent (via completing the PCF—online supplemental appendix 2) and complete their baseline assessment to inform them of their group allocation. Table 1 describes the physiotherapist-led triage and treatment service and usual care group.

**Table 1 T1:** Physiotherapist-led triage and treatment service and usual care protocol.

Treatment group and subgroup	Intervention protocol
Physiotherapist-led triage and treatment service	
*All participants*	For participants randomised to the physiotherapist-led triage and treatment service, the screening physiotherapist will match them to different modes and types of care during the call informing participants of their group allocation.
*Low risk* of poor outcomes	Participants at low risk of poor outcomes (Keele STarT MSK tool score 0–4)^28^ will be offered brief advice and education (via one telephone call with a physiotherapist) including advice on activity modification, analgesia if necessary and education that their condition has a good prognosis. This advice and education will be provided during the phone call where participants are informed of their trial arm allocation. Participants in this treatment subgroup will be asked to call the screening physiotherapist back if their symptoms have not improved in 6 weeks. If nil contact is received after 6 weeks, participants will be discharged from the physiotherapy service.
*Medium risk* of poor outcomes or requiring postoperative rehabilitation	Participants at medium risk of poor outcomes (Keele STarT MSK tool score 5–8) or requiring postoperative rehabilitation will be offered physiotherapy via telehealth. An appointment with a telehealth physiotherapist will be organised by the screening physiotherapist during the phone call where participants are informed of their trial arm allocation. Telehealth physiotherapy will consist of assessment, advice, education to support self-management and a tailored home-exercise programme delivered via the PhysioTherapy Exercise App (freely available online exercise prescribing software created by some of the study authors: www.physiotherapyexercises.com). The number of appointments offered will be at the discretion of the treating physiotherapist.
*High risk* of poor outcomes and/or with potential nonprogressive radiculopathy	Participants at high risk of poor outcomes (Keele STarT MSK tool score 9–12) and/or with potential nonprogressive radiculopathy will be offered a course of clinic-based (in-person) physiotherapy as is usually provided at the participating public hospital clinics. An appointment with a clinic-based physiotherapist will be organised by the screening physiotherapist during the phone call where participants are informed of their trial arm allocation. Participants will be offered clinic-based care but will not be told they are at high risk of poor outcomes (according to the Keele STarT MSK tool). Clinic-based physiotherapy may include a combination of any advice and education to support self-management (eg, advice to exercise, modify activities, lose weight or take simple pain medications if needed), exercise tailored to patients’ activity goals and level of function, graded activity, graded exposure and manual therapy. The number of appointments offered will be at the discretion of the treating physiotherapist.
Usual care	
All participants	Participants randomised to the usual care group will be offered a course of clinic-based (in-person) physiotherapy as is usually provided at the participating public hospital clinics and an initial appointment commensurate with the usual clinic waiting time. An appointment with a clinic-based physiotherapist will be organised by the screening physiotherapist during the phone call where participants are informed of their trial arm allocation. Participants will be offered clinic-based physiotherapy which may include a combination of any advice and education to support self-management (eg, advice to exercise, modify activities, lose weight or take simple pain medications if needed), exercise tailored to patients’ activity goals and level of function, graded activity, graded exposure and manual therapy. The number of clinic-based appointments will be at the discretion of the treating physiotherapist.
Participants in either group can be referred to a specialist pain clinic or to see a psychologist if the treating physiotherapist believes it would be valuable. All treatment for participants in both trial arms will be conducted within weekday business hours (Monday to Friday from 7.30 a.m. to 4.30 p.m.). Waiting time includes weekends and public holidays when the clinics are closed as it is the normal approach to reporting waiting time in participating clinics.	

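### Blocks of 2 and 4 within site-by-subgroup strata leave some allocations predictable to the role that both screens and announces the arm, and the three subgroups used as strata overlap

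*Protocol article*

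**What the plan says.** The Randomisation procedure section describes how the list is made: "The 1:1 random allocation sequence will be independently generated in Stata by the team’s biostatistician and uploaded to REDCap". On blocking it states: "The randomisation sequence will use randomly permuted blocks of variable sizes (2 and 4) to ensure equal numbers in both groups". It then names the factors that form the strata: "Stratification variables for the randomisation sequence include trial sites and the three treatment subgroups". The abstract gives the number of sites: participants are "recruited from six public hospitals located in metropolitan Sydney, Australia". Randomisation procedure also says that the sequence is concealed from on-site staff and that the current participant's arm stays hidden until baseline data are in REDCap.

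Participant recruitment gives eligibility to the screening physiotherapist: "the screening physiotherapist will explain the trial and determine their eligibility using a screening form that contains the eligibility criteria". Randomisation procedure gives the same role the call that announces the arm: "The screening physiotherapist will telephone participants who consent". Under Blinding, therapists and assessors are not blinded.

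Table 1 defines the subgroups. Low risk is a Keele STarT MSK score of 0–4. The medium row reads: "Participants at medium risk of poor outcomes (Keele STarT MSK tool score 5–8) or requiring postoperative rehabilitation will be offered physiotherapy via telehealth". The high row, where care is in the clinic, begins: "Participants at high risk of poor outcomes (Keele STarT MSK tool score 9–12) and/or with potential nonprogressive radiculopathy will be offered". The article states no order of precedence. Under Primary analysis, subgroup is a covariate in both coprimary models.

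**The concern.** Concealing the list does not stop a recruiter inferring the next arm from arms already announced. Short blocks within many small strata keep each stratum close to balance, so the arm that is behind is usually the next one assigned. A recruiter who anticipates the arm could, without meaning to, encourage or delay entry of patients thought unsuited to telephone care or to a long wait. The groups could then differ in ways that adjustment for baseline function, site and subgroup does not remove.

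The overlap is a separate problem. The stratum must be settled before each randomisation, and the same variable enters the models and determines the mode of care in the intervention arm. If a participant fits two rows, the stratum depends on who classifies. It also touches the waiting-time outcome: a telephone contact counts as a first appointment, and low-risk intervention participants are treated in the allocation call, whereas the other two subgroups have an appointment booked during it.

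**Working it through.** **Inputs.** 1:1 allocation, block sizes 2 and 4, strata of site by three subgroups (Randomisation procedure); six sites (abstract); 368 participants (Sample size). Strata: 6 × 3 = 18, so 368 / 18 ≈ 20 participants each. The mix of block sizes is not stated; I assume both are equally likely and show the range.

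**The plan's own figure.** The plan gives none for predictability. The total of 368, used here only as an input, reproduces: for a margin of 0.7, SD 1.9, two-sided 5% and 90% power, a t-based calculation needs 156 per arm; 156 / 0.85 = 183.5, so 184 per arm and 368 in total.

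**Correct guesses, completed blocks.** Rule: guess the arm that is behind in the stratum and toss a coin when tied. It needs no knowledge of block size.
- Block of 2: 0.5 + 1 = 1.5 correct; 1.5 / 2 = 75.0%.
- Block of 4, six equally likely orders: the two orders opening with the same arm twice (AABB, BBAA) give 0.5 + 0 + 1 + 1 = 2.5; the other four give 0.5 + 1 + 0.5 + 1 = 3. Mean (2 × 2.5 + 4 × 3) / 6 = 2.833; 2.833 / 4 = 70.8%.
- Equal mix: (1.5 + 2.833) / (2 + 4) = 72.2%. Any mix lies between 70.8% and 75.0%.

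**Certain allocations.** If a balanced stratum is followed by the same arm twice, the block must be one of 4 and the next two allocations are known. This happens in 2 of 6 blocks of 4. Per block of 2 plus block of 4 (six participants): (1/3 × 2) / 6 = 11.1%. Unfinished blocks lower this slightly.

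**Simulation.** Strata of 20, equally likely block sizes, best guess from stratum history; ranges are across repeat runs.

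| Block sizes | Correct | Certain |
|---|---|---|
| 2, 4 | 71.8–71.9% | 10.2–10.6% |
| 4, 6 | 68.4% | 5.7% |
| 4, 6, 8 | 67.1–67.3% | 2.2–2.5% |

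**What the recruiter knows.** 368 participants over 18 strata, 1,000 runs.

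| Knowledge | Blocks 2, 4 | Blocks 4, 6, 8 |
|---|---|---|
| Stratum and its full history | 71.5% | 66.9% |
| Site balance only | 63% | 60% |
| Two recruiters per site, each knowing only their own calls | 56% | 56% |

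**Overlap.** Applying the Table 1 rows as printed:

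| Participant | Low | Medium | High |
|---|---|---|---|
| Postoperative, score 0–4 | yes | yes | no |
| Postoperative, score 9–12 | no | yes | yes |
| Postoperative with radiculopathy, score 5–8 | no | yes | yes |
| Radiculopathy, not postoperative, score 0–4 | yes | no | yes |
| Radiculopathy, not postoperative, score 5–8 | no | yes | yes |

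The abstract words the subgroups with the same overlap. The number affected cannot be derived, because no shares are given. As an illustration only, if 30% were postoperative and 25% of those scored 9–12, the count would be 368 × 0.30 × 0.25 ≈ 28. With assumed shares from 10% and 10% up to 40% and 30%, it runs from about 4 to about 44.

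**The case against.** **Predictability.** A reader might infer that seven in ten allocations are known in advance to a recruiter who sees every earlier one. The document does not support that. The 72% is an average success rate against 50% by chance; only about 10% are certain. Access to data refers to screening physiotherapists in the plural, and neither the number per site nor any sharing of records is stated. Eligibility is judged in the first call, before the baseline questionnaire is sent, so the STarT MSK stratum is usually unknown then unless the referral suggests it (postoperative, for example). On the email or SMS route participants consent and complete baseline themselves, and others may be randomised in between. These points stand, and they are why 63% and 56% belong beside 72%. They do not remove the risk: the screening physiotherapist offers help with the questionnaire and receives posted forms, so can know the answers before they are entered. A reader might also infer that both coprimary outcomes are biased; nothing shows that selection occurred, and no size of bias can be given.

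Longer blocks also lower the average guess by only about 5 points, and hiding the sizes does not affect that average. That stands; the main gain is in certain allocations.

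**Overlap.** The postoperative and radiculopathy phrases may be meant to override the score, which would settle the participants who meet only one of them. That reading is nowhere stated, and it does not settle a postoperative participant who scores 9–12 or has radiculopathy. The article is condensed, Figure 1 is not shown, and the model of care is described elsewhere, so a precedence rule may exist. It would be too strong to say that the trial has none; the point is that the definitions as printed conflict. Since stratification requires a classification before allocation, any misclassification of the stratum should mainly add noise rather than differ by arm.

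**Conclusion.** Both parts hold, at moderate weight. With blocks of 2 and 4 in about 18 strata, an unblinded role that screens and announces can guess the next arm correctly about 72% of the time and be certain for about 10%, provided that one person knows the stratum and its full history and that block sizes are equally likely. With less knowledge the success rate is about 63% or 56%. This is an avoidable weakness in concealment, not evidence of selection.

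The three subgroups used as stratification factor, covariate and basis for the mode of care are not mutually exclusive as printed. The clearest conflict is a postoperative participant who scores 9–12 or has potential nonprogressive radiculopathy. How many participants this covers is unknown.

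**What to change.** 1. For the remaining sequence, drop blocks of 2 and use larger random sizes, for example 4, 6 and 8, not disclosed to screeners. Certain allocations fall from about 10% to about 2%, and best-case correct guesses from about 72% to about 67%.
2. Reconcile the Table 1 rows, and the matching text in the abstract, so that each participant falls in exactly one subgroup. Record that subgroup in REDCap before randomisation in both arms, and use the recorded value as the covariate. The planned models already adjust for subgroup, so only its source needs stating. Which pathway applies to overlapping participants is for the investigators.

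Cost: a new list segment, a wording change, and Steering Committee and ethics approval of the amendment. Larger blocks allow slightly more imbalance in small strata, which the planned adjustment for site and subgroup handles. Recruitment was planned for September 2024 to December 2025, and the article does not show how much of the sequence remains; if recruitment has closed, the first item no longer applies and the second reduces to documenting how overlapping participants were classified.
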